#### Data analysis

Piecewise linear mixed effect models will be used as the primary analysis method, with correlations between repeated measurements taken into account. The mean and standard deviation of the pre-intervention slope (-6 to 0 months) and post intervention slope (0 to 12 months) as well as the mean outcome measure at time 0 with 95% Confidence Interval will be estimated. The difference of the two slopes will be tested based on the Z score at the significance level of two-sided 0.05. The model will be fitted with and without covariates. Piecewise least squares analysis will be conducted as supportive analysis. The primary analysis will be performed on the qualified intention to treat (ITT) population of all the clients enrolled in this study. Missing outcome data will be handled by the mixed effect model approach, providing the missing at random (MAR) assumption is met. If appropriate, multiple imputation will be used to generate missing covariate data. Quantitative process evaluation data shall be described. Qualitative process evaluation data shall be described and where appropriate, thematically analysed. Where possible, analyses will also be conducted using process evaluation data as predictors of outcomes.

An estimate of LEAP program costs will be made. This will be based on the costs of both delivering and staff attending the training, time for the LEAP champion, and the cost of any materials or resources required for activities.

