## Methods/design

The design of the program was informed by Greenhalgh’s framework for diffusion of innovations in service organisations [26] and the literature on implementation and culture change in health and aged care [27-35]. Cost, scalability and sustainability were also considerations of the program design. We did not specifically base the program design on a theory, as there was no published theory that appeared suitable with a sound evidence base in predicting good implementation outcomes [36]. The three components of the program are:

1) Engaging site management and care staff with the LEAP for Life program

2) Employing a LEAP champion one day a week at each site

3) A training program (detailed below)

The program logic model of the implementation is outlined in Figure 1. LEAP will encourage case managers to include social and recreational goals in client care plans; and care workers to increase behaviours which engage clients socially and recreationally. Behavioural change of care workers and case managers is to be driven by a LEAP champion within each site. By increasing client engagement, we hypothesise that client depression, loneliness, apathy and/or agitation will improve for those with symptoms in these areas, and that satisfaction with care will also increase. We also hypothesise that relationships between care staff and clients, and care staff work satisfaction will increase.

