### Setting

The project will be evaluated with five aged care community service providers in regional and metropolitan New South Wales, Australia. The providers were approached to participate by the chief investigator. Two of the sites specifically provide services for clients from ethnic minority, non-English speaking backgrounds. These services deliver case managed home care packages. The types of services provided by these packages include personal care, domestic assistance, social support, travel to appointments, in-home respite and nursing care.

Eligibility criteria for participating services are:

• Government accredited, providing home care packages to older people in the community;

• Not enrolled in another intervention study relating to engagement and activities;

• Willing to sign a legal contract with regards to program terms.

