### Design

LEAP is being evaluated using a quasi-experimental design with measurements taken at -6, 0 (baseline immediately pre-intervention), 6 and 12 months. The time period from -6 to 0 months will act as non-intervention comparison for the period between 0, 6 and 12 months. Clients will be clustered under their case managers (*n* = 20).

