##### Secondary outcome measures

Secondary outcome assessment tools for both client and care worker are detailed in Table 2.

**Table 2 T2:** Secondary outcome measures for client and care staff and the covariates

	**Measure**	**Data collection method**
Client secondary outcome		
Agitation	34-item Cohen-Mansfield Agitation Inventory-relative[62]	Family self-report
	13-item Agitation subscale of The Neuropsychiatric Inventory – Clinician Rating Scale [63]*	Client/family interview
Dysphoria/depression	15-item Geriatric Depression Scale [64]^†^	Client self-report
	13-item Dysphoria subscale of The Neuropsychiatric Inventory- Clinician Rating Scale [63]*	Client/family interview
Loneliness	20-item Revised UCLA Loneliness Scale [65]‡	Client self-report
Apathy	18-item Apathy Evaluation Scale – self and informant [66]	Client and family self-reports
	11-item Apathy subscale of The Neuropsychiatric Inventory - Clinician Rating Scale [63]*	Client/family interview
Satisfaction with care	9-item care worker subscale and 13-item case manager subscale of the Home Care Satisfaction Measure [67]	Client self-report
Client Covariates	age; gender; care site; hours and type (i.e. CACP, EACH or EACH-D) of packaged care; duration of package; the presence (or absence) of a cohabiting carer; number and hours of care from non-paid carers; dementia or mental health diagnoses; ethnicity; language spoken; education; previous employment; significant life events/functional change as reported by case manager; case manager; client and care worker positive interaction measured by the 8-item positive relationship subscale of the Caregiver Interaction Scale completed by the family [68]; happiness measured by the 8-item Jovality subscale and 4-item attentiveness subscale of the PANAS-X client self-report (completed once in reference to the time scale of the past two weeks and once in reference to during care worker visits) [62]; severity of cognitive impairment as measured by the Global Deterioration Scale [69]; two items assessing importance to client and family that care workers engage socially with the client; country of birth; years lived in Australia; English proficiency; income; living situation; relationship of family member; relationship between care worker and client as measured by the 4-item Bond subscale of the Working Alliance Inventory Short Form client report [70]	Client/family self-report
		Care plan audit
		Case manager interview
		Client/family interview

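### The primary slope test makes no stated provision for change that is shared within case managers or sites, and its Z reference is too liberal for 20 clusters

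*Protocol article*

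**What the plan says.** The Data analysis section of the protocol article fixes the primary model and the dependence it handles: "Piecewise linear mixed effect models will be used as the primary analysis method, with correlations between repeated measurements taken into account". It also fixes the test: "The difference of the two slopes will be tested based on the Z score at the significance level of two-sided 0.05". On adjustment it says "The model will be fitted with and without covariates", without naming either fit as primary.

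The cluster structure is described elsewhere. The Design section says "Clients will be clustered under their case managers" and puts their number at 20; the Power section repeats this for the 211 target clients. Under Setting, "The project will be evaluated with five aged care community service providers". The program components in Methods/design include "Employing a LEAP champion one day a week at each site", and the same section makes that champion the driver of behaviour change among care workers and case managers.

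Site and case manager both appear among the client covariates in Table 2: "age; gender; care site; hours and type" and, later in the same list, "significant life events/functional change as reported by case manager; case manager; client and care worker positive interaction". They would therefore enter the fit with covariates.

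**The concern.** The article twice declares that clients are grouped under case managers. It then describes a primary analysis whose only named dependence is that between one client's repeated measurements, and refers the result to a normal distribution.

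The quantity tested is a change in slope. A case manager whose clients always score high or low does little harm, because a constant shift largely drops out of the contrast. The harm comes if clients of the same case manager or site change together. That is plausible here: uptake may be uneven between champions and case managers, time trends may be shared within a service, and the care workers who complete the engagement questionnaire may rate more than one client. Entering case manager and site as main-effect covariates removes differences in level; it does not correct the standard error for slopes that vary by cluster.

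At stake is the 5% level of the main test, and the coverage of its interval, in a design that the Discussion section itself describes as non-controlled.

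**Working it through.** **Inputs from the protocol article.** 211 clients, 20 case managers, d = 0.2, two-sided 0.05, pre-post correlation 0.5 (Power); 5 sites (Setting). **Assumed:** ICC of client-level change, 0 to 0.10; the article gives none. Its 0.5 is a correlation between pre and post measures within a client, not within a case manager.

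**1. The plan's own power figure.** For one group measured before and after, the SD of change = √(2(1 − 0.5)) = 1. Required n = ((1.960 + 0.842) × 1 / 0.2)² = 196.2, so 197 clients. At 211 clients, power is 82.8% (normal) or 82.4% (noncentral t). The claim of 80% or more is reproduced, but with a design effect (DE) of 1. Under the normal approximation, 80% survives up to DE = 211 × 0.2² / 2.802² = 1.075, that is, ICC = 0.075 / 9.55 ≈ 0.008. The named clustering does not enter this figure.

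**2. Size of a Z test that ignores clustering.** With equal clusters, DE = 1 + (m − 1) × ICC, and true size = 2 × (1 − Φ(1.96/√DE)). Here m = 211/20 = 10.55 per case manager or 211/5 = 42.2 per site. Example: ICC 0.05 at case-manager level gives DE = 1 + 9.55 × 0.05 = 1.48, √DE = 1.22 and size 10.7%.

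| ICC of change | DE, 20 case managers | True SE / naive SE | True size | DE, 5 sites | True size |
|---|---|---|---|---|---|
| 0 | 1.00 | 1.00 | 5.0% | 1.00 | 5.0% |
| 0.01 | 1.10 | 1.05 | 6.1% | 1.41 | 9.9% |
| 0.02 | 1.19 | 1.09 | 7.3% | 1.82 | 14.7% |
| 0.05 | 1.48 | 1.22 | 10.7% | 3.06 | 26.3% |
| 0.10 | 1.96 | 1.40 | 16.1% | 5.12 | 38.6% |

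A simulation with 40,000 runs per setting agrees: 5.1%, 6.2%, 7.4%, 10.9% and 16.5% for case managers, and 14.8% for sites at ICC 0.02.

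**3. The Z reference on its own.** If clustering is modelled but 1.96 is kept, P(|t| > 1.96) on 19 df is 6.5%; the correct cut-off is 2.09. With 5 clusters (4 df) the size is about 12%; the cut-off is 2.78. In the simulation with 20 clusters, cluster means tested against 1.96 rejected in 6.4% to 6.5% of runs, and against t on 19 df in 4.9% to 5.0%.

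**4. Power once clustering is respected.** For the pre-post contrast of the Power section, with 211 clients and t on 19 df, the noncentrality is 0.2 × √(211/DE). For ICC 0.01 / 0.02 / 0.05 / 0.10, power is 75% / 71% / 62% / 51%. These values refer to the plan's own power contrast, not to the slope difference.

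**The case against.** A condensed article commonly leaves the random-effects structure to a fuller document, and this one does not spell out even the client effects. Saying that repeated-measurement correlation is handled does not say that other correlation is excluded. The fit with covariates, which holds case manager and site, is planned and not optional. A reader might therefore infer too much in concluding that the plan rejects clustering, and the text does not support that. What it does support is narrower: the one dependence it names and the Z reference it fixes do not cover clustered change, and main-effect covariates would not repair this.

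Each client is also their own comparison, so stable cluster differences largely cancel, and with an ICC of change of 0 there is no inflation. This stands; the result is conditional.

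If LEAP had no effect anywhere, its route of delivery alone would create no variation in change. This also stands. Inflation under that strict null needs shared time trends or shared raters. Uneven delivery still matters when the average effect is zero but effects differ by cluster, and for the coverage of the interval around any average effect.

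Finally, the services were approached by the chief investigator and were not sampled, so one could treat these clusters as the whole target. The abstract, however, looks to the community setting in general, which calls for inference beyond these 20 case managers.

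**Conclusion.** The point holds in conditional form. The stated primary model and test make no provision for change shared within case managers or sites. If such sharing exists, the standard error is too small. The loss ranges from nothing (ICC 0) to a true size of about 16% (ICC 0.10) at case-manager level, and is about 15% at site level for an ICC of 0.02. These sizes rest on assumed ICCs and equal cluster sizes.

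A reader might infer that the intervals are certainly too narrow and the 5% level already lost. The document does not show that: it gives no ICC of change, and the size of the problem cannot be derived from it. The Z reference is a lesser fault, about 6.5% against 5% with 20 clusters, and it applies once cluster-level degrees of freedom are the relevant ones.

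**What to change.** In the Data analysis section:

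- Add to the client-level terms a case-manager random intercept and a random slope change, or use a cluster-robust variance with a small-sample correction.
- Test the slope difference against a t reference with cluster-based degrees of freedom (Kenward-Roger or Satterthwaite) instead of Z. If the variance components cannot be estimated, average the client contrasts within each case manager and use a t test on 19 df.
- Say which fit, with or without covariates, is primary.
- Handle site through site-by-slope terms or a site-level sensitivity analysis. A site main effect alone is only a level shift. Acknowledge that inference across five sites stays weak under any method.
- Add care worker as a crossed effect for the care-worker-rated score only if a care-worker identifier is recorded; Table 2 does not list one.

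Case manager and site are already listed in Table 2, so those parts need no new data. The cost is precision. At case-manager level, the interval is about 1.12 / 1.17 / 1.30 / 1.49 times as wide as the naive one for ICC 0.01 / 0.02 / 0.05 / 0.10 (√DE × 2.09/1.96). Power falls below the stated 80%, to about 75% to 51% over that range, and the Power section should say so.

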## Discussion

LEAP for Life is a pragmatic program with the aim of increasing engagement of aged care clients by aged care staff. The program is designed to be economical to deliver and self-sustaining after the implementation period, and is being evaluated in the real world setting.

The non-controlled design means that we cannot with certainty attribute any observed changes to the LEAP program. However it is unlikely that care worker behaviour with relation to clients would systematically be affected by external factors. The detailed process evaluation will also add confidence in attributing the change to the implementation processes, as well as in understanding the mechanisms and processes involved in changing home care staff behaviour.
